### Sample Size

With the recruitment of a sample size of 352 participants and anticipated 80% retention over time, tests for effects of the interventions will have a power of 0.80 or greater for a type I error of 0.05 to detect a difference of 0.35 SDs in the mean quality of life and depressive symptoms and of 35% in ART adherence and viral suppression between participants receiving versus not receiving each intervention at each follow-up assessment. A higher retention rate will increase power to detect smaller effects.

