### Statistical Analysis

We will describe demographic characteristics for the sample and baseline levels of all primary and secondary outcomes. We will use ANOVA and chi-square tests to assess baseline differences in demographics and outcomes for those assigned to the 4 conditions. If significant differences between conditions exist, these will be accounted for in the primary analyses. Finally, we will assess possible sample attrition bias by examining demographic characteristics associated with loss to follow-up and by comparing retention across the 4 conditions.

We will use an intent-to-treat approach when analyzing outcomes [55]. The focus will be on the main effects of each intervention. We will use generalized linear mixed models (GLMMs) to test the impact of each intervention on the primary outcomes of viral suppression, ART adherence, quality of life, and depressive symptoms over time. This approach will test hypotheses within a repeated measures framework, with an individual identifier included in the models as a random effect to account for the correlation between participants’ outcomes over time. We will test hypotheses that the social support intervention and the SBCM intervention increase the likelihood of viral suppression and ART adherence, improve quality of life, and reduce depressive symptoms at 4-, 8-, and 12-month follow-ups, compared to not receiving each intervention, by examining the main effect of each intervention. The impact on viral suppression will be evaluated at 4 and 12 months only. GLMMs will also test the 2-way interaction between the interventions to understand whether the interventions are enhanced or offset by one another. If any differences between the randomized conditions emerge in preliminary analyses, covariates will be included in the models to account for these differences; similarly, if any covariates are associated with retention in the study, these covariates will be included in the models to improve the handling of missing data. Separate GLMMs will evaluate each hypothesis, with appropriate link functions used for binary outcomes (viral suppression and adherence) and continuous outcomes (quality of life and depressive symptoms). Hypotheses will be tested at the *P*<.05 level.

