The same approach will be used to test the impact of each intervention on the secondary outcomes of social support, loneliness, stigma, self-efficacy, service use, and structural barriers. We will test hypotheses that the social support intervention and the SBCM intervention increase social support, self-efficacy, and uptake of needed services as well as decrease loneliness, stigma, and structural barriers at 4-, 8-, and 12-month follow-ups, compared to not receiving each intervention, by examining the main effect of each intervention.

Exploratory analyses will assess whether intervention effects differ based on demographic characteristics—including sex, race, and age (age 50-64 y vs age >65 y)—and baseline engagement in care (low vs high). Moderation analyses will shed light on who most benefits from the intervention programs, which can help guide better targeting of the programs or future efforts to refine and tailor interventions to meet the needs of any who do not benefit. We will test moderation by introducing interaction terms into the GLMM models assessing primary and secondary outcomes. In separate models for each moderator and outcome, we will include interactions between the moderator and assignment to each intervention as predictors of outcomes. Significant interaction terms will indicate differing intervention effects across subgroups. Significant interaction terms will be “plotted and probed” to examine intervention effects within different subgroups of participants [56].

Additional exploratory analyses will test whether the amount of each intervention received (ie, the number of sessions attended) or the mode of intervention delivery (ie, Zoom [Zoom Video Communications, Inc] vs telephone) relate to outcomes. These analyses will include only those participants randomly assigned to receive each intervention. GLMM models will examine associations between the number of intervention sessions attended or mode of intervention delivery (predictors) and outcomes (viral suppression, ART adherence, quality of life, and depressive symptoms), controlling for demographic covariates as needed. Separate models will estimate dose-response and mode-response relationships for each intervention-outcome combination.

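### For viral suppression and adherence, a model interaction term alone decides interaction and moderation, and it cannot by itself show who gains most in absolute terms

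*Protocol article*

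**What the plan says.** All statements are in the Statistical Analysis section of the protocol article's Methods.

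- **Model.** Each primary outcome has its own generalized linear mixed model (GLMM) with the participant as a random effect, "with appropriate link functions used for binary outcomes (viral suppression and adherence". No link is named, and no effect measure for reporting is fixed.
- **Two-intervention interaction.** The GLMMs test the two-way term "to understand whether the interventions are enhanced or offset by one another". Hypotheses are tested at P<.05.
- **Moderation.** Interactions of each intervention with sex, race, age group and baseline engagement in care (low or high) are added in separate models. The rule is: "Significant interaction terms will indicate differing intervention effects across subgroups". Only terms that pass are plotted and examined within subgroups; the plotting scale is not given. These analyses are labelled exploratory.
- **Use.** The moderation results are meant to show who benefits most and to help target or refine the programs.

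The Sample Size section states the binary target as a difference "of 35% in ART adherence and viral suppression between participants receiving versus not receiving each intervention at each follow-up assessment". It gives no comparison rate and does not say whether the 35% is absolute or relative.

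**The concern.** With a nonlinear link, a model interaction compares effects on the link scale. Under logit it compares odds ratios, and with a participant random effect these are odds ratios at a fixed value of that effect. Who benefits most, read as a targeting question, asks in which subgroup more people become suppressed or adherent. The two answers diverge when subgroups start from different rates, most of all when one is near the ceiling.

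Baseline engagement in care is likely to separate participants in just this way: the Limitations section expects the sample to include people with suboptimal adherence and detectable viral loads beside better-engaged ones. If the odds ratios match, the term will tend to be non-significant, the printed rule then calls for no plot, and a several-fold difference in people helped could be read as no moderation. Equal absolute gains can, conversely, appear as an interaction. The same ambiguity affects the reading of the two-intervention term as enhancement or offset.

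**Working it through.** **1. The plan's own figure.** Inputs from Sample Size: "With the recruitment of a sample size of 352 participants and anticipated 80% retention over time"; power of at least 0.80 at a type I error of 0.05 (two-sided assumed); 0.35 SD for the continuous outcomes. Per level of each factor, n = 352 × 0.80 / 2 = 140.8. The standardized distance is 0.35 × √(140.8/2) = 2.94, and the power is Φ(2.94 − 1.96) ≈ 0.836. The continuous statement reproduces as a floor. The binary statement cannot be checked, because neither a comparison rate nor the meaning of 35% is given. All rates below are therefore assumptions.

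**2. Model for the check.** Logit link (assumed), random intercept u ~ N(0, s²). The proportion in a group with intercept a is P(a) = E[expit(a + s·u/s)], that is, expit(a + u) averaged over u, computed by Gauss-Hermite quadrature. Solve P(a) = p₀ for the rate without the intervention, then p₁ = P(a + ln OR) and the risk difference is p₁ − p₀.

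**3. One common conditional odds ratio of 2 (zero interaction on the link scale).** For s = 2 the latent intraclass correlation is 4/(4 + π²/3) = 0.55.

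- At 60%: a = 0.668; a + 0.693 gives p₁ = 69.7%, a gain of 9.7 points.
- At 95%: a = 4.422; a + 0.693 gives p₁ = 97.1%, a gain of 2.1 points.

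| Random-intercept SD | Gain at 60% | Gain at 95% | Ratio |
|---|---|---|---|
| 0 | 15.0 | 2.4 | 6.1 |
| 1 | 12.8 | 2.3 | 5.5 |
| 2 | 9.7 | 2.1 | 4.7 |
| 3 | 7.5 | 1.7 | 4.4 |

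The ratios use unrounded gains. The row with SD 0 has no random effect, so it does not describe the planned model. With a conditional odds ratio of 2.5 and SD 2, the gains at 50%, 70% and 90% are 13.6, 10.7 and 4.7 points.

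**4. The converse.** The same 8-point gain is a population odds ratio of 1.38 at 50%, 1.52 at 70%, 1.83 at 80% and 5.44 at 90%. Equal absolute benefit can look like moderation.

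**5. Two interventions together.** Suppose each alone moves 80% to 88%. Without a random effect, the odds are 4 × 1.833 × 1.833 = 13.4, so no interaction means 93.1% with both. At SD 2 it means 93.3%. Simple addition would give 96%, which the model would show as an interaction odds ratio of 1.79 (SD 0) or 2.01 (SD 2), readable as enhancement although the gains only add.

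**The case against.** The strongest case against is that the article condenses a fuller plan. It names no link, fixes no reporting measure and excludes none, and the choice of effect measure normally belongs in a statistical analysis plan, which is not shown. That stands for the main effects: the absence of a risk difference there is no finding.

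Several stronger readings are tempting, and the document supports none of them.

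- A reader might infer that effects will be reported only as log odds ratios. The text does not say so, and follow-up plots could show predicted probabilities.
- A reader might call the conditional odds ratio inflated. For 85% against 92%, the population odds ratio is 2.03 and the conditional one is 2.7 at SD 2. That is a different estimand, not a biased estimate. With no intervention effect both are null, so the gap does not invalidate the main-effect tests.
- A reader might say the link scale is the wrong one. Interaction depends on scale whichever is chosen, and the link scale is legitimate. The wording about enhancing or offsetting does not commit the trial to additivity.
- A reader might quote a sixfold contrast. That holds only with no random effect.

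It is also fair that moderation is exploratory and that main effects are the declared focus. What the objection does not meet is the printed rule: significance of the term decides moderation, and only significant terms get the follow-up. That step therefore cannot reveal unequal absolute gains behind a non-significant term. The plot rule is printed for moderators only, not for the two-intervention term.

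**Conclusion.** The point holds in a limited form. For the two binary primary outcomes, the stated rule for moderation, and the test for the two-intervention interaction, rest on a link-scale term that does not by itself show who benefits most in absolute terms, which is the use the article gives to moderation. For a common conditional odds ratio of 2, the absolute gain at a 60% rate is 4.4 to 5.5 times that at 95% for random-intercept SDs of 3 down to 1 (9.7 against 2.1 points at SD 2). This rests on an assumed logit link, assumed rates and assumed SDs; the document gives none of them. The direction holds at every SD tried, but the actual size in this trial is unknown. No primary conclusion is put at risk. It is an improvement worth making because it lets the trial answer its own targeting question.

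**What to change.** Keep the GLMMs and all planned tests. For viral suppression and for adherence, add to the plan:

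1. Average the model's predictions over the random effect and over the sample, to give standardized proportions by assignment to each intervention, with the risk difference and its CI (delta method or bootstrap).
2. Do the same for the four combinations of the two interventions, and report the interaction as a difference in risk differences beside the interaction odds ratio.
3. Within each level of every pre-specified moderator, report the standardized proportions, the risk differences and their contrast with CIs, whether or not the link-scale term is significant.
4. Name the link, and say that the model odds ratios are conditional on the participant.

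The cost is a post-estimation step on models already planned. It also adds exploratory estimates, many with wide intervals, which must be labelled as such. The Results section puts analysis after follow-up ends in April 2027, so this can be specified beforehand.

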#### Supportive-Expressive Peer Social Support Groups Intervention

This program, adapted from Project Linkage [25], is delivered to groups of approximately 8 to 12 participants by trained facilitators from the Southern AIDS Coalition. The groups meet weekly for 90-minute sessions over 8 weeks. Participants may choose to join each session by videoconference with or without video, or they may join by telephone for an audio-only experience. Each session has a unique focus: (1) introductions, program overview, and establishing group rules and expectations; (2) feelings around HIV diagnosis, stigma, and questions of “why did HIV happen to me?”; (3) values and priorities in life and thoughts about mortality; (4) uncertainty, challenges, and lack of control; (5) physician-patient relationship; (6) friend and family relationships; (7) body image and sense of self; and (8) reflection, summary, and closure. On the basis of participant feedback during our pilot, we incorporated the topic of HIV-related stigma into this intervention and also recruited group facilitators who had more shared lived experiences with participants. After the 8 group meetings, participants in groups are offered the opportunity to share their contact information with other participants if they are interested and sent instructions on how to host their own videoconference meetings should they wish to continue meeting to provide mutual social support.

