#### SBCM Intervention

This adapted individually tailored SBCM intervention [21] is delivered by telephone or video by trained research staff over 5 sessions. The first session lasts 45 to 60 minutes and is focused on the following: (1) developing facilitator-participant rapport; (2) discussing participants’ background, current needs, and life challenges (eg, transportation, food insecurity, insurance, mental health, or technology); (3) identifying and ranking life challenges that participants experience as stressors and barriers to HIV care or quality of life; (4) identifying 1 stressor to focus on for the remaining sessions; (5) discussing past strategies to deal with the stressor; and (6) setting a short-term goal related to the stressor. After the first session, the facilitator compiles and sends the participant relevant, individually tailored resources (local and online) to aid in addressing contextual factors related to the stressor of focus. During the second session of similar length, the facilitator and participant will (1) review the resource list; (2) assess progress toward the short-term goal; (3) talk about accomplishments, strengths, and skills the participant has identified in their own life; and (4) revise the strategy to achieve the participant’s goals, incorporating identified strengths and skills to support progress. The final 3 sessions are optional, brief (15-30 min) check-ins, occurring at 1- to 2-week intervals, as determined by the participant and facilitator. These sessions focus on the achievement of an intermediate or long-term goal via the same collaborative process carried out in the first 2 sessions.

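### The exploratory dose and mode models name only demographic adjusters, so baseline differences in the outcome can appear as, or mask, a dose or mode association

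*Protocol article*

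**What the plan says.** All places are in the Protocol article.

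- **Purpose and status** (Statistical Analysis): "Additional exploratory analyses will test whether the amount of each intervention received", or the mode of delivery, is related to outcomes. The analyses are labelled exploratory.
- **Population** (same paragraph): "These analyses will include only those participants randomly assigned to receive each intervention". There is no randomized comparison within this group.
- **Adjustment** (same paragraph): the models relate sessions attended or mode to "outcomes (viral suppression, ART adherence, quality of life, and depressive symptoms), controlling for demographic covariates as needed".
- **Target** (same paragraph): the text speaks of associations but closes with "Separate models will estimate dose-response and mode-response relationships for each intervention-outcome combination".
- **How dose arises** (SBCM Intervention): "The final 3 sessions are optional, brief (15-30 min) check-ins, occurring at 1- to 2-week intervals, as determined by the participant and facilitator".
- **How mode arises** (Supportive-Expressive Peer Social Support Groups Intervention): "Participants may choose to join each session by videoconference with or without video, or they may join by telephone for an audio-only experience". For SBCM, delivery is by telephone or video, and the text does not say who chooses.
- **What is available** (Measures and Table 1): all four primary outcomes are measured at baseline. The covariate rows cover demographics, socioeconomic position and health, geography, and use of other services. No baseline outcome score is among them.

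**The concern.** Among people assigned to the same intervention, those who attend more sessions, or who join by video, may have differed at baseline in depressive symptoms, adherence or quality of life. The article's own background makes this plausible. Its interviews name depression as a barrier to care engagement, and its survey of 446 people links low engagement to lack of internet access, lower income and higher stress. Baseline and follow-up values of the same outcome are normally correlated, so a model without the baseline value can attribute that difference to dose or mode.

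The bias could go either way. If healthier or more motivated people attend more, a benefit of dose can appear where none exists. If people with more need take up the optional SBCM sessions, a real benefit can be hidden or look like harm. At stake is the reading of these exploratory results. The trial's test of efficacy is not involved.

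**Working it through.** **1. The plan's own figure.** The article gives no figure for the dose and mode models. Its Sample Size section gives 352 participants, 80% retention, type I error 0.05 (taken as two-sided), a difference of 0.35 SD and power of at least 0.80. Allocation is equal, so each level of a factor has 352 × 0.8 / 2 = 140.8 analysed. Noncentrality is 0.35 × √(140.8/2) = 2.94, and power is Φ(2.94 − 1.96) = 0.836. The stated figure is reproduced. The same arithmetic gives about 141 analysed participants for each dose or mode model.

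**2. Set-up, with no true dose effect.** Let u be the baseline outcome, x the attendance and y one continuous follow-up, all standardized. Let r = corr(x, u) and ρ = corr(u, y), with no path from x to y. Then corr(x, y) = r × ρ, which is also the spurious slope when u is omitted. Both r and ρ are assumptions; the ranges used are r from 0 to 0.3 (and −0.2) and ρ from 0.5 to 0.7.

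**3. Check by Fisher z.** The test statistic has mean atanh(rρ) × √(141 − 3) = atanh(rρ) × 11.75.
- r = 0.2, ρ = 0.5: rρ = 0.10, mean 1.18, rejection probability Φ(1.18 − 1.96) + Φ(−1.18 − 1.96) ≈ 0.22.
- r = 0.3, ρ = 0.7: rρ = 0.21, mean 2.50, rejection probability ≈ 0.71.

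**4. Simulation** (4,000 runs per scenario, n = 141, linear regression without the baseline outcome). Mode is a 50:50 split of a latent variable that has correlation r with baseline. Entries are false-positive rates for ρ = 0.5 / 0.6 / 0.7.

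| r | Spurious slope for dose (r × ρ) | Dose | Mode |
|---|---|---|---|
| 0 | 0 | 0.05 / 0.05 / 0.05 | 0.05 / 0.06 / 0.05 |
| 0.1 | 0.05 to 0.07 | 0.09 / 0.11 / 0.12 | 0.08 / 0.09 / 0.11 |
| 0.2 | 0.10 to 0.14 | 0.22 / 0.30 / 0.39 | 0.15 / 0.21 / 0.26 |
| 0.3 | 0.15 to 0.21 | 0.43 / 0.58 / 0.70 | 0.31 / 0.41 / 0.52 |
| −0.2 | −0.10 to −0.14 | 0.21 / 0.29 / 0.39 | 0.15 / 0.19 / 0.26 |

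The dose column agrees with the Fisher z values. The last row shows the same inflation with the sign reversed.

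**5. With the baseline outcome added.** The false-positive rate is 0.046 to 0.062 across all scenarios, and every mean slope is within 0.007 of zero. This removes only the confounding that runs through the measured baseline outcome.

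**The case against.** The case for leaving the plan alone has several parts.

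- **The analyses are exploratory, and the text already speaks of associations.** This is right and keeps the point minor. The closing sentence on dose-response and mode-response relationships still claims more, and neither that paragraph nor the Limitations section mentions self-selection.
- **A condensed article leaves covariate lists to the analysis plan.** This is a fair caution. The wording does not say that demographics are the only adjusters, and Table 1 groups demographics with health items such as comorbid conditions and survey mode. But the article does name an adjustment set, and the baseline outcome is not in it or in Table 1's covariates.
- **The calculation is not the planned model.** This stands. It uses one continuous follow-up, whereas the plan uses repeated-measures GLMMs and two of the four outcomes are binary, so the rates do not carry over directly to viral suppression or adherence. If baseline entered as a repeated outcome with a dose-by-time term, baseline differences would be partly absorbed. No such term is stated, and the article tests its main hypotheses through main effects.
- **The correlations are assumed.** This stands too. At zero correlation there is no inflation, and at 0.1 it is small.

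A reader might infer more than the article supports: that these models will produce false dose effects, that SBCM participants choose their mode, that mode must be coded as one fixed variable per person, or that the results will set the number of sessions for roll-out. The first needs a correlation that the article does not give. Chosen mode is documented only for the support groups. The coding of mode across sessions is not fixed. No section ties the recommended number of sessions to these analyses.

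**Conclusion.** The concern holds in a limited form. The exposures are not randomized, and the adjusters named for these models omit a baseline measure that the trial collects. A baseline difference can therefore create or mask a dose or mode association, in a direction that cannot be known in advance.

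For dose, the false-positive rate runs from the nominal 5% to 70% over the assumed range; for mode it reaches 52%. These figures rest on the assumed correlations, about 141 analysed participants per intervention, a single continuous follow-up and no true effect. They show what modest selection can do. They do not predict what the trial will find.

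This is a minor point about exploratory analyses. The intent-to-treat comparisons of each intervention are untouched.

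**What to change.** 1. In every dose and mode model, always include the baseline value of the outcome. Add baseline variables likely to predict attendance or mode that the article already plans to collect or use: engagement in care (a planned moderator), structural barriers, use of other services, and web versus paper survey completion.
2. Replace the closing sentence on estimating dose-response and mode-response relationships with wording that reports non-causal associations. State that unmeasured need or motivation may remain after adjustment.
3. Optionally, add a sensitivity analysis that reports the optional SBCM sessions separately from the core ones. This is a preference and not a correction.

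The cost is a few lines of analysis text and slightly larger models. No new data are needed, and the change can be made before follow-up ends, which the Results section places by April 2027.
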